## Abstract

**Background:**

Despite the capability of emergency surgery to reduce the mortality of severe spontaneous intracranial hemorrhage (SSICH) patients, the effect and safety of surgical treatment for severe spontaneous intracranial hemorrhage (SSICH) patients receiving long-term oral antiplatelet treatment (LOAPT) remains unclear. In consideration of this, the cohort study is aimed at figuring out the effect and safety of emergency surgery for SSICH patients on LOAPT.

**Methods:**

As a multicenter and prospective cohort study, it will be conducted across 7 representative clinical centers. Starting in September 2019, the observation is scheduled to be completed by December 2022, with a total of 450 SSICH patients recruited. The information on clinical, radiological, and laboratory practices will be recorded objectively. All of the patients will be monitored until death or 6 months after the occurrence of primary hemorrhage.

**Results:**

In this study, two comparative cohorts and an observational cohort will be set up. The primary outcome is the effect of emergency surgery, which is subject to assessment using the total mortality and comparison in the survival rate of SSICH patients on LOAPT between surgical treatment and conservative treatment. The second outcome is the safety of surgery, with the postoperative hemorrhagic complication which is compared between the operated SSICH patients on and not on LOAPT. Based on the observation of the characteristics and outcome of SSICH patients on LOAPT, the ischemic events after discontinuing LOAPT will be further addressed, and the coagulation function assessment system for operated SSICH patients on LOAPT will be established.

**Conclusions:**

In this study, we will investigate the effect and safety of emergency surgery for SSICH patients on LOAPT, which will provide an evidence for management in the future.

**Ethics and dissemination:**

The research protocol and informed consent in this study were approved by the Institutional Review Board of Beijing Tiantan Hospital (KY2019-096-02). The results of this study are expected to be disseminated in peer-reviewed journals in 2023.

**Trial registration:**

Name: Effect and safety of surgical intervention for severe spontaneous intracerebral hemorrhage patients on long-term oral antiplatelet treatment.

ChiCTR1900024406. Date of registration is July 10, 2019.

## Background

With high mortality and morbidity, spontaneous intracerebral hemorrhage is acute, severe hemorrhagic stroke [1]. For the patients suffering from severe spontaneous intracerebral hemorrhage (SSICH), emergency surgery may provide a means of saving their life [1–7]. Over the past few decades, the morbidity of such ischemia diseases as coronary heart disease has been on the increase with population aging, which may leave nearly a quarter of spontaneous intracerebral hemorrhage patients needing long-term oral antiplatelet treatment (LOAPT) [8]. However, the emergency surgery intended for patients on LOAPT carries a high level of risk to develop intraoperative and postoperative hemorrhagic complications [9, 10]. Up to now, the relative evidences were given only for selective operation, which recommended discontinuation of antiplatelet medications before surgery [1, 9, 11–15], which may hinder emergency surgery for SSICH patients on LOAPT; thus, there was no evidence about the emergency surgery for SSICH patients on LOAPT. Due to the rapid progression of SSICH and the potential risk of newly emerging and re-emerging ischemic events, however, it is usually impossible to discontinue antiplatelet treatment until coagulation function is restored. Once these complications occur, the patients would be faced with an even more catastrophic consequence [16]. Therefore, it is imperative for neurosurgeries and neurologists to develop an appropriate treatment strategy for SSICH patients on LOAPT.

Meanwhile, it is worth noting that there is still no effective strategy developed to assess the coagulation function of surgical patients on LOAPT. Given antiplatelet medication can have a significant impact on hemostasis and coagulation, the risk of intraoperative hemorrhage and postoperative intracranial bleeding (PIB) is a major focus because they can cause fatality [1, 2]. Though the preoperative screening of coagulation function could be effective in protecting patients from developing hemorrhagic complications, those commonly used methods are not applicable to assess the coagulation function of patients on LOAPT as the antiplatelet medication mainly affects platelet function, rather than clotting factors. Notably, there are various tools, such as thromboelastogram (TEG), reported to aid medical professionals in assessing the platelet function in the cardiac surgery and intracranial traumatic injury [17, 18]. Therefore, they have a potential to assist with the development of suitable treatment strategy for SSICH patients on LOAPT.

In addition to hemorrhagic complications, ischemic complications are also a problem worthy of consideration during the management of SSICH patients on LOAPT due to the hypercoagulable state caused by discontinuing antiplatelet medications. Besides, even though patients are stable after receiving appropriate treatment, it remains debatable to resume antiplatelet treatment. Therefore, there are many SSICH patients who have a history of antiplatelet treatment still stopping antiplatelet treatment after primary hemorrhage, which makes them under high risk of ischemic complications.

According to a previous study, the outcome after spontaneous intracerebral hemorrhage is poor, and the mortality could exceed 30% [1, 19]. Nevertheless, considering a lack of clarity on the effect and safety of emergency surgery for SSICH patients on LOAPT, there is no evidence gathered to support clinical decision-making. Therefore, a prospective cohort study will be conducted to investigate the safety and effect of emergency surgery for SSICH patients on LOAPT, based on which a scientific strategy will be proposed for the selection of an appropriate treatment.

## Methods

### Study design

Surgical treatment for antiplatelet intracerebral hemorrhage (SAP-ICH) is an ongoing and multicenter study; the flow chart of which is shown in Fig. 1. Beginning in September 2019, this trial is scheduled to be completed by December 2022. Due to unknown and hugely potential intracranial hemorrhage complications after neurosurgery, ethical issues need to be taken into account; therefore, the randomized controlled trial was not suitable currently. The purpose of this study is to evaluate the effect and safety of emergency surgery for SSICH patients on LOAPT, with the focus placed on four aspects: (1) the outcome of operated SSICH patients on LOAPT; (2) the risk of intraoperative and postoperative hemorrhagic complications; (3) the risk of developing postoperative ischemic diseases for SSICH patients on LOAPT; (4) the methods to assess the coagulation state of operated SSICH patients on LOAPT.

**Fig. 1 Fig1:**
[figure not shown]
Research flow chart

In order to achieve the research objective, it is necessary to recruit all SSICH patients except those not on LOAPT receiving conservative treatment. The inclusion and exclusion criteria are detailed in Tables 1 and 2, respectively. Three cohorts, including two comparative groups and one observational group (Fig. 1), will be established. Firstly, in order to measure the effect of emergency surgery, a comparison will be drawn of the outcomes and complications between SSICH patients on LOAPT receiving emergency surgery and those receiving conservative treatment. Secondly, in order to evaluate the safety of emergency surgery, hemorrhagic complications will be compared between operated SSICH patients who are on LOAPT and those not on LOAPT. Thirdly, the clinical characteristics and coagulation function of SSICH patients on LOAPT will be analyzed to assess the risk of developing ischemic diseases after discontinuing antiplatelet treatment, based on which an effective approach to the assessment of coagulation state will be established for surgery.

**Table 1 Tab1:** Inclusion criteria

Inclusion criteria: (1) 18–75 years old; (2) non-traumatic intracerebral hemorrhage; (3) severe intracerebral hemorrhage, which was defined as patients with supratentorial bleeding volume > 30 ml, infratentorial bleeding volume > 10 ml, midline shift > 1 cm, or large intraventricular hematoma; (4) Glasgow coma score (GCS) < 13; (5) family members agree to provide an informed written consent.

**Table 2 Tab2:** Exclusion criteria

Exclusion criteria: (1) patients had cerebrovascular diseases, e.g., intracranial aneurysm or vascular malformation, and intracranial tumors, which were associated with hemorrhage; (2) hemorrhagic transformation of cerebral infarction; (3) hemorrhage caused by venous thrombosis; (4) patients with severe coagulation disorder, e.g., hemophilia; (5) patients with coagulation dysfunction caused by malignant tumor, hypohepatia, renal dysfunction, thrombocytopenia, coagulation diseases, and so on; (6) patients receiving other anticoagulation medications (vitamin K antagonist and new oral anticoagulants); (7) patients not on LOAPT who receive conservative treatment; (8) the patients who died before or on arriving at the hospital and within a short period (6 h) after admission.	

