### Outcomes and study endpoints

All patients will be closely monitored until death or 6 months after the occurrence primary hemorrhage. In this study, the following outcomes will be taken into consideration (Table 3). The primary outcome is the total mortality, including in-hospital and out-of-hospital mortality. The second outcome is the postoperative hemorrhagic complication, and the PIB is our main focus. The functional outcome of patients is another outcome interesting us and will be assessed using modified Rankin scale (mRS). The postoperative adverse cardiovascular/cerebral events (ACCE) include the region of original stroke enlarging, new ischemic stroke occurring outside the operative region, myocardial infarction, repeated revascularization, and deep venous thrombus. The screening, evaluation, and follow-up schedules are detailed in Table 4.

**Table 3 Tab3:** Outcomes to be taken in consideration

(1) Total mortality; (2) postoperative hemorrhagic complication; (3) patients’ functional outcome; (4) postoperative adverse cardiovascular/cerebral events (ACCE).

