### Study definition

After admission, all of the patients would receive standardized care according to the guidelines. Severe spontaneous intracerebral hemorrhage (SSICH) is confirmed by both severe intracerebral hemorrhage radiologically and clinical coma (GCS < 13).

In definition, “on long-term oral antiplatelet therapy (on LOAPT)” refers to patients that received oral antiplatelet treatment on a continued basis for more than 7 days and discontinued antiplatelet medication no more than 7 days after the occurrence of hemorrhage. Antiplatelet therapy involved aspirin, clopidogrel, and dual antiplatelet treatment. Postoperative intracerebral bleeding (PIB) was defined as rehemorrhage within the operative region or new intracerebral hemorrhage associated with the operation on radiological examination.

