### Data collection

In case the patients meet our criteria, all information, including the demography, clinical information, preoperative radiological data, intraoperative findings, and laboratory and TEG data, will be recorded on the case report form (CRF). After being discharged, all the patients were followed up on a regular basis by outpatient visit and on telephone 3 months and 6 months after primary hemorrhage, respectively. During each follow-up visit, the survival condition, mRS, ACCE, and medication will be recorded. If the patients feel unable to undergo radiological examination in the participating center, a follow-up cranial image will be required. Once radiological examination is completed, the patients’ imaging data will be transmitted to the Tiantan hospital (this center will work as an imaging interpretation center) to reconfirm several events, including SSICH, PIB, and postoperative ischemic disease. During the study, the researchers are required to protect privacy for the patients and ensure the confidentiality of their medical information. The information collection schedule is presented in Table 4.

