## Results

China National Clinical Research Center for Neurological Diseases will be responsible for data analysis. Sample size was calculated by using PASS (Version 15, NCSS corporation, American). All sample size calculations were performed by conducting two-sided test, *α* = 0.05 and *β* = 80% (the degree of control = 80%). In this study, two comparison groups will be established, with the primary and secondary outcomes as the focus in this study. According to our unpublished data collected from 7 participating centers in 2019, for SSICH patients on LOAPT, the total mortality was about 30% for operated patients and 45% for the patients receiving conservative treatment, with the ratio of two groups reaching about 1:1.5. Moreover, for operated SSICH patients, the incidence of PIB was about 23% for patients on LOAPT and 10% for patient not on LOAPT, with the ratio of two groups reaching about 1:2.5. With regard to the primary outcome, our sample size was calculated as 196 (196 SSICH patients on LOAPT, operation group: *n* = 78; conservation group: *n* = 118). As for the secondary outcome, the sample size was 247 (247 operated SSICH patients, LOAPT group: *n* = 70; non-LOAPT group: *n* = 177). Moreover, in order to establish the coagulation function assessment system, the area under curve was expected to be 0.7, and the sample size was set to 92 (92 operated SSICH patients on LOAPT, PIB group: *n* = 23; non-PIB group: *n* = 69). In this case, a minimum of 387 SSICH patients (includes 118 patients on LOAPT receiving conservative treatment, 92 patients on LOAPT receiving emergency surgery, and 177 patients not on LOAPT receiving emergency surgery) may be required in this study to reach our research objective. Thus, to ensure final statistics, a total of 400 patients (patients on LOAPT receiving conservative treatment, *n* = 120; patients on LOAPT receiving emergency surgery, *n* = 100; patients not on LOAPT receiving emergency surgery, *n* = 180; Fig. 1) will be recruited. In this study, 10% of patients would be lost during follow-up. Finally, we decided to recruit 450 appropriate patients.

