All statistical analyses were conducted with the assistance of SPSS (Version 22.0, IBM, American). The data was indicated as mean (x) ± standard deviation (SD) for normally distributed data, median, and interquartile range (IQR) for skewed distributed data or number (*n*) and percentage (%). In this study, two main comparative groups and an observational cohort will be established, as shown in Fig. 1. Firstly, in order to investigate the effect of emergency neurosurgery, a comparison will be performed between SSICH patients on LOAPT receiving conservative treatment and those receiving emergency neurosurgery. Secondly, in order to investigate the safety of emergency neurosurgery, a comparison will be performed between operated SSICH patients on LOAPT and those not on LOAPT. Thirdly, in order to investigate the intra/postoperative complications and the risk of ischemic disease after discontinuing antiplatelet treatment, the characteristics of SSICH patients on LOAPT will be analyzed; moreover, because the history of previous neural ischemic events or cardiac events could affect the risk of postoperative ischemic events, we would perform the subgroup analysis depending on this history to further investigate the effect of discontinuing antiplatelet treatment on the risk of ischemic disease. The difference will be compared by conducting χ^2^ test, Mann-Whitney *U* tests, or Student’s *t* tests. The independent risk factors were analyzed by logistic regression, while the factors with *p* < 0.10 in univariate analysis were entered into a multivariate logistic regression model. The result was indicated as odd ratio (OR) and 95% confident interval (CI). The receiver operating characteristic (ROC) curve analysis was performed to test the prediction value of different parameters and different methods. An area under the curve (AUC) in a ROC analysis of ≥ 0.7 is considered as a clinical utility, while *p* value of < 0.05 was treated as statistically significant.

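### The conservative group in the primary mortality comparison can include patients whose active care was limited at the treatment decision, and the stated design does not separate them

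*Protocol article*

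**What the plan says.** Under Study design, the protocol article sets the recruitment scope: "it is necessary to recruit all SSICH patients except those not on LOAPT receiving conservative treatment". It then defines the effect comparison by treatment received: "a comparison will be drawn of the outcomes and complications between SSICH patients on LOAPT receiving emergency surgery and those receiving conservative treatment".

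Tables 1 and 2 list five inclusion and eight exclusion criteria. None concerns declined surgery, limited care or withdrawn care. The nearest is exclusion (8), which removes "the patients who died before or on arriving at the hospital and within a short period (6 h) after admission".

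Under Outcomes and study endpoints: "The primary outcome is the total mortality, including in-hospital and out-of-hospital mortality". Follow-up runs to death or 6 months.

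On care, Study definition says: "After admission, all of the patients would receive standardized care according to the guidelines". Ethics and public involvement leaves treatment to the usual clinical course. The Discussion gives drug examples of conservative treatment and lists the indications for surgery among the questions the study will not resolve.

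On data, Data collection says that "all information, including the demography, clinical information, preoperative radiological data, intraoperative findings, and laboratory and TEG data, will be recorded" on the case report form. On analysis, the Results section plans a chi-square test and a logistic regression in which factors with p < 0.10 "in univariate analysis were entered into a multivariate logistic regression model". The sample size rests on earlier data from the centres in which "the total mortality was about 30% for operated patients and 45% for the patients receiving conservative treatment".

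**The concern.** These are patients with severe hemorrhage and a GCS below 13. Some may be unoperated because the team and family chose active medical treatment. Others may be unoperated because the case was judged unsalvageable or the family declined active care. The stated grouping puts both kinds into one conservative group, and no stated rule fixes why a patient is not operated.

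Limiting care acts directly on all-cause mortality, which is the primary outcome. If care-limited patients are more common among the unoperated, part of any survival difference reflects the decision to limit care and not the absence of surgery. The planned regression would not reliably remove this: severity covariates may pick up part of it, but not the decision itself. If the decision is not recorded, a reader cannot tell how much of a difference comes this way.

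**Working it through.** **1. Does the stated design admit these patients?** Take an unoperated patient on antiplatelet therapy whose active care was limited at the treatment decision.
- Inclusion (1) to (5): met, if the patient is aged 18–75, the hemorrhage is severe, the GCS is below 13 and the family consents to the study.
- Exclusions (1) to (6): these concern the cause of the bleed, coagulation disorders and anticoagulants. They may remove some poor-prognosis patients but do not address care goals.
- Exclusion (7): does not apply, because the patient is on antiplatelet therapy.
- Exclusion (8): does not apply once the patient survives 6 hours.

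So the patient is recruited and falls into the conservative group.

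**2. Inputs for an illustration.**
- From the Results section: 30% mortality in operated and 45% in conservative patients; planned groups of 100 and 120; two-sided alpha of 0.05.
- Assumed, not in the document: no effect of surgery; 30% mortality under active care in both groups; mortality m under limited care (95%, or 90% as a variant); care-limited shares s_cons and s_op in the conservative and operated groups.

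**3. The plan's own figure.** The article states 196 patients (78 and 118) for 30% versus 45%. The two-sided pooled formula at 80% power and a ratio of 1:1.5 gives 137 + 206 = 343, and 78 versus 118 has about 56% power. The stated number is not reproduced. That is a separate matter, and nothing here rests on it. At the planned 100 versus 120, power for 30% versus 45% is about 63%.

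**4. Spurious difference** = (s_cons − s_op) × (m − 0.30). The last column is the exact binomial probability that the two-sided 5% chi-square test, on 100 versus 120 patients, favours surgery (nominal 2.5%).

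| m | s_cons | s_op | Difference | Test favours surgery |
|---|---|---|---|---|
| 0.95 | 0.10 | 0 | 0.10 × 0.65 = 6.5 points | 17.1% |
| 0.95 | 0.20 | 0 | 0.20 × 0.65 = 13 points | 51.5% |
| 0.95 | 0.10 | 0.05 | 0.05 × 0.65 = 3.25 points | 7.2% |
| 0.95 | 0.20 | 0.05 | 0.15 × 0.65 = 9.75 points | 31.8% |
| 0.90 | 0.10 | 0 | 0.10 × 0.60 = 6 points | about 15% |
| 0.90 | 0.20 | 0 | 0.20 × 0.60 = 12 points | about 46% |
| any | equal | equal | 0 points | nominal |

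In a conservative group of 120, shares of 10% and 20% are 12 and 24 patients.

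**5. A channel in the other direction.** Suppose instead that 20% of the conservative group are milder patients with 10% mortality (assumed). The bias is 0.20 × (0.10 − 0.30) = −4 points, against surgery.

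**6. Both channels together, still with no effect of surgery.** With 10% care-limited and 20% milder:
- All conservative patients: 0.10 × 0.95 + 0.20 × 0.10 + 0.70 × 0.30 = 0.325, a difference of +2.5 points.
- Restricted to patients without care limitation: (0.02 + 0.21) / 0.90 = 0.256, a difference of −4.4 points.

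Here the restricted estimate lies further from the truth than the all-patient one. Restriction removes one channel and exposes the other.

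**7. What a rule requiring both analyses to be significant would cost.** Suppose 45% is the true overall conservative mortality and 5% or 10% of that group is care-limited at 95% mortality. The remaining mortality is (0.45 − 0.05 × 0.95) / 0.95 = 42.4%, or (0.45 − 0.10 × 0.95) / 0.90 = 39.4%. The chance that both tests favour surgery falls from about 63% to about 47% or 30%.

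**The case against.** The document does not say that care-limited patients are recruited, how many there are, or that they cluster among the unoperated. The shares and the 90–95% mortality are assumptions. Study definition promises guideline care to all, and the Discussion's examples of conservative treatment are active drug therapy. Read together, these suggest an actively treated comparator. The age cap, family consent and the 6-hour exclusion narrow the channel further. The listed data items are not exhaustive, the schedule in Table 4 is not visible, and an article commonly leaves case report form fields and sensitivity analyses to the full documents.

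Much of this stands. It limits the size of the channel and means that non-recording cannot be asserted. It does not remove the point. The entry criteria and the comparison are stated, and neither a general sentence on care nor drug examples in a Discussion assign a care-limited patient to a group or keep that patient out.

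A reader might go further and infer that the comparison is biased towards surgery overall, or that the anticipated 15-point gap is an artefact. The documents support neither. They give no share of care-limited patients, and other confounding by indication can act against surgery, as step 6 shows. Nor do they support making a survival claim conditional on both analyses: that is a trade-off with a heavy power cost, and restriction can itself mislead. Where limitation reflects severity, it may drop the sickest unoperated patients while keeping equally sick operated ones.

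**Conclusion.** The point holds in conditional form. As stated, the primary mortality comparison counts care-limited unoperated patients who survive 6 hours, with family consent, as conservatively treated. If they are more common in that group than among the operated, this channel favours surgery.

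Its size is unknown. Under the assumptions in the working it ranges from 0 points with equal shares to 13 points with a 20% share in the conservative group only. The direction applies to this channel alone; the net bias of the whole comparison is unknown. Whether the case report form already captures the decision cannot be judged from the article. This is a cheap and worthwhile improvement, not proof that the planned result would be wrong.

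**What to change.** If the case report form does not already do so, record in both groups:
- any decision to limit active care at or before the decision whether to operate;
- the reason surgery was not done (for example not indicated, judged unsalvageable, family refusal).

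Keep the all-patient comparison as primary. Beside it, report the number of care-limited patients per group and a supportive sensitivity analysis of total mortality restricted in both groups to patients with no such decision. Adjust that analysis for baseline severity, for example GCS, hematoma volume and age. If the two estimates diverge, interpret a survival difference as an effect of surgery with caution. Do not require both to be significant.

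The cost is a little extra data entry, and chart review for patients already enrolled. Recruitment and the primary population do not change. Two limits remain: care limitation may be documented unevenly between groups, and restriction can bias against surgery. The restricted analysis should therefore stay supportive only.

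### Grouping by treatment received, with follow-up from the haemorrhage, counts waiting deaths after hour 6 as conservative and biases the mortality comparison towards surgery

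*Protocol article*

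**What the plan says.** All of the following is in the protocol article.

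- **Groups.** Study design defines the effect comparison as "between SSICH patients on LOAPT receiving emergency surgery and those receiving conservative treatment". The statistical part of the Results section repeats this split. Neither place refers to the strategy chosen or to the time of the decision.
- **Outcome and clock.** Under Outcomes and study endpoints: "The primary outcome is the total mortality, including in-hospital and out-of-hospital mortality". Also: "All patients will be closely monitored until death or 6 months after the occurrence primary hemorrhage". The follow-up period is tied to the haemorrhage, not to surgery or to a treatment decision.
- **Early deaths.** Table 2, item 8 excludes "the patients who died before or on arriving at the hospital and within a short period (6 h) after admission".
- **Analysis.** "The difference will be compared by conducting χ^2^ test, Mann-Whitney *U* tests, or Student’s *t* tests". Logistic regression follows, on factors selected by univariate screening. The abstract mentions a comparison of survival, but the statistical text names no time-to-event, time-dependent or landmark method.
- **Design.** Treatment is not randomised: "therefore, the randomized controlled trial was not suitable currently".
- **Planned difference.** The sample-size paragraph assumes mortality of 30% operated and 45% conservative, at a ratio of 1:1.5.

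**The concern.** Membership of the surgical group depends on something that happens during follow-up: reaching theatre alive. The time between eligibility and incision is free of death for operated patients by construction. Unoperated patients have no such protection. A patient meant for surgery who dies first adds a death to the conservative group and takes one away from the surgical group.

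The article itself describes severe haemorrhage as progressing rapidly, and its Background says that advice to stop antiplatelet drugs before surgery may hinder emergency operation. Death before theatre is therefore plausible in this population. The error lies in how exposure is assigned over time, so logistic regression on baseline factors cannot correct it. At stake is the primary result, which could show a survival benefit that comes partly from the labelling.

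**Working it through.** **Reference figure.** The plan gives no figure for this bias. The yardstick is its planned difference: 45% − 30% = 15 percentage points.

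**Where each LOAPT patient lands under the text**

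| Course after admission | Primary comparison |
|---|---|
| Dies within 6 h, operated or not | Excluded (Table 2, item 8) |
| Survives 6 h, is operated at any time | Surgical |
| Survives 6 h, meant for surgery, dies first | Conservative (inferred: no other group exists) |
| Survives 6 h, never meant for surgery | Conservative |

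Item 8 takes waiting deaths in the first 6 h out of both groups, which limits the bias. Waiting deaths after hour 6 remain. Item 8 also takes out any patient operated on early who dies within 6 h of admission, although the outcome is total mortality.

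**Size when surgery has no effect.** The article gives neither time to surgery nor the number of waiting deaths, so these inputs are assumptions:

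- 6-month mortality after hour 6: m = 0.40, whatever the treatment.
- Share meant for surgery: q = 0.45.
- Death times from hour 6 are Weibull with cumulative hazard H(t) = 0.511 × (t/180 days)^k, where 0.511 = −ln 0.60. Shapes k = 0.3, 0.4 and 0.5 give 1 − exp(−H(1 day)) = 10%, 6% and 4% dying in the 24 h after hour 6.
- Waits to surgery are exponential with mean w.

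Let f be the share of surgical candidates who survive 6 h but die before theatre, that is, the mean of 1 − exp(−H(wait)) over the waits. Then:

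- operated mortality = (m − f)/(1 − f)
- conservative mortality = [m(1 − q) + qf]/[(1 − q) + qf]

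*All waits start at hour 6 (nobody operated earlier).* For k = 0.3 and w = 24 h, f = 0.0916:

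- operated: 0.3084/0.9084 = 33.9%
- conservative: (0.22 + 0.0412)/(0.55 + 0.0412) = 44.2%
- difference: 10.2 points

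*Waits start at admission.* Only a share exp(−6/w) is still waiting at hour 6, so f is multiplied by that share. For k = 0.3 and w = 24 h, f = 0.0916 × 0.779 = 0.0713:

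- operated: 0.3287/0.9287 = 35.4%
- conservative: (0.22 + 0.0321)/(0.55 + 0.0321) = 43.3%
- difference: 7.9 points

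Spurious benefit in percentage points:

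| Clock and mean wait | 10% die in 24 h | 6% | 4% |
|---|---|---|---|
| From admission, 3 h | 0.7 | 0.4 | 0.2 |
| From admission, 6 h | 2.5 | 1.3 | 0.7 |
| From admission, 12 h | 5.0 | 2.8 | 1.6 |
| From admission, 24 h | 7.9 | 4.7 | 2.8 |
| From hour 6, 6 h | 6.8 | 3.5 | 1.8 |
| From hour 6, 12 h | 8.3 | 4.6 | 2.6 |
| From hour 6, 24 h | 10.2 | 6.1 | 3.6 |

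**Simple cross-check.** Take the pooled mortality (0.30 + 1.5 × 0.45)/2.5 = 39% in both groups, with 100 patients meant for surgery and 120 for conservative care. If 2 of the 100 die waiting, the result is 37/98 = 37.8% against 48.8/122 = 40.0%, about 2 points. If 5 die waiting, it is 34/95 = 35.8% against 51.8/125 = 41.4%, about 6 points.

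**The case against.** **The classification is inferred.** No sentence says where a patient accepted for surgery who dies first is counted. The flow chart and schedule are not shown, and a full protocol or SAP may settle it. This stands as a caveat. But the article does state the group definition, the exclusion, the follow-up period and the tests, and together these leave such a patient only one group. The point rests on what the article fixes, not on what it omits.

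**Emergency surgery may come early.** If mean waits from admission are 6 h or less, the spurious benefit is at most about 2.5 points. This stands, and it is why the range starts near zero. The figures near 10 need every operation to fall after hour 6, which the article does not say.

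**Stronger readings that the documents do not support**

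- A reader might infer that the 6 h exclusion creates the bias. It does not: it removes the earliest waiting deaths and so reduces the problem.
- A reader might infer that the planned 15-point difference is itself an artefact. Returning about 12 of the 53 conservative deaths (0.45 × 118) to the surgical side would erase it: (23.4 + 12)/(78 + 12) = 39% against (53.1 − 12)/(118 − 12) = 39%. That shows sensitivity only. Nothing in the article says how many such deaths occurred.
- A reader might assume that 10-15% of surgical candidates die waiting after hour 6, which gives 12-18 points in the cross-check. No source supports those shares, and the largest f in the scenarios above is 9%.

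**Conclusion.** The point holds. As written, the primary mortality comparison is biased in favour of surgery, because operated patients must survive to incision while unoperated deaths after hour 6 fall to the conservative group. The direction follows from the stated design, given the inferred classification of waiting deaths.

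The size cannot be determined from the documents. Under the assumptions above it is about 0-8 percentage points for mean waits of 3-24 h from admission, and up to about 10 if all surgery follows hour 6, against 15 planned. It could be negligible or more than half of the effect sought.

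The 6 h exclusion is a partial safeguard, not the cause. Its separate cost is that any surgical death within 6 h of admission leaves an outcome described as total mortality. The change should be made before analysis.

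**What to change.** - **Primary analysis.** Keep the 6 h rule and make it time zero: start the analysis clock at 6 h after admission. Treat surgery as a time-dependent exposure, so that each patient counts as unoperated until incision. Patients already operated on by hour 6 enter as operated.
- **Sensitivity analysis.** Add a landmark analysis at 6 h, with groups defined by whether surgery had started by then.
- **Reporting.** Give the number of deaths within 6 h of admission by whether surgery had started, where screening records allow.

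**Cost.** No patient's care or recruitment changes. Times of surgery and death must be recorded, and the model is slightly more complex than a χ² test or logistic regression. The count of early deaths is more than a change of wording: under Data collection, case report forms are completed for patients who meet the criteria, so deaths within 6 h may not be on file. The apparent benefit of surgery may shrink. Confounding by indication is a separate problem that this change does not solve.
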